### Study Procedures

#### Randomization

We will randomize 144 participants with an equal allocation ratio of 1:1 to receive either VDOT or UC-DOT. An equal allocation was chosen to optimize the power of the study [30]. Permuted block randomization with block sizes of 4 and 6 will be used to allocate participants to intervention or control groups while maintaining balance across groups. Each block will have a specified number of randomly ordered treatment assignments [30]. Additionally, stratified randomization will be done according to sex to ensure equal representation of men and women in each study group [30]. The stratification is justified because sex is an important variable that influences adherence to TB treatment [31]. A computer program will randomly generate study arm assignments within block sizes of 4 and 6. This randomization will minimize the likelihood that the study team will be able to predict the next study arm assignment. Each block will contain equal proportions of control and intervention. Within each block will be 4 or 6 sealed, opaque allocation envelopes, depending on the block size. Blocks and allocation envelopes will be sequentially numbered according to the computer-generated randomization schedule. Each allocation envelope will contain an assignment card on which the study group assignment (UC-DOT or VDOT) will be printed. To assign a patient to a study group, blocks will be selected in their sequential order. Allocation envelopes within them will be selected sequentially as well. Each envelope will be opened only after the participant details have been written on it. Carbon paper inside the envelope will transfer participants’ details to the assignment card. Allocation envelopes will be sealed using tamper-proof security tape.

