### Sample Size

This trial is powered on the primary outcome measure and based on a comparison of the medication adherence level between the UC-DOT group and the VDOT group. The calculated sample size is 124 in order to achieve a chi-square test difference of 0.85 versus 0.63 (difference 0.22 and odds ratio 0.30) between the groups. We assumed an attrition rate of 14%, guided by published literature; this was based on a randomized controlled trial comparing a digital adherence intervention and usual care in Kenya in which the overall loss to follow-up rate was 11.7% (9.9% in the usual-care DOT arm and 1.76% in the digital intervention arm) [38]. By inflating the attrition rate to 14%, we erred on the higher side of attrition. In contrast, another RCT of asynchronous VDOT done in the United Kingdom had a higher attrition rate of 23%; however, the study population was very different from our current study in that it included 58% of homeless subjects [15]. At a 14% attrition rate, the estimated final sample size was 144 participants with 72 subjects per group. This would provide a power of 80% to detect a 22% difference in the primary outcome between the 2 comparison groups (85% VDOT vs 63% DOT) based on a 2-sided significance level of 5%. Sample size tables were used to estimate precision. All calculations were performed using the SAS statistical software package (version 9.3; SAS Institute).

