Univariate statistics will be used to describe the baseline characteristics of the study population, the prevalence of individual clinical responses, and the level of adherence. Similar analyses will be repeated for secondary outcomes. Multivariable logistic regression analyses will be done to test for significant associations between study groups (VDOT/ UC-DOT) as the main exposure and the primary binary outcome of adherence (≥80%; yes/no). Age and HIV status are set a priori as potential confounders that will be adjusted for in all the models. Sex will not be adjusted since the randomization is stratified by sex. Other covariates that will be adjusted for in the models include education level, income, and smartphone ownership, previous TB treatment, HIV status, and other clinical variables at baseline. Crude and adjusted odds ratios with 95% confidence intervals will be presented, and statistically significant *P* values will be less than .05.

Secondary analyses of time-to-treatment completion will provide another outcome that can be used to compare the 2 groups according to TB program performance indicators. Survival analysis to compare the median time-to-treatment completion between study groups with associated log-rank tests will be performed. Crude and adjusted Cox proportional hazards regression analyses will be performed to determine factors associated with time-to-treatment completion. Cox proportional hazards ratios with corresponding 95% confidence intervals will be presented. Other analyses comparing trends at months 2, 4, and 6 in adherence, sputum conversion, and clinical response will be performed. These repeated measures data will be modeled as a discrete-time Markov chain or Poisson process [30]. Analyses will be done using Stata (version 14; StataCorp) and R (version 3.3.2; R Core Team) software.

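### Stratifying randomization by sex is given as the reason to leave sex out of the models; the reasoning is backwards, and the cost is a mildly conservative test and a little lost power

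*Protocol article*

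**What the plan says.** The Randomization section of the protocol article plans permuted blocks of 4 and 6, allocated 1:1 and stratified by sex, on the ground that "sex is an important variable that influences adherence to TB treatment".

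The Statistical Analyses section then sets the rule for the models: "Sex will not be adjusted since the randomization is stratified by sex". The same paragraph adjusts for age and HIV status in all models, and for education, income, smartphone ownership, previous TB treatment and other baseline clinical variables. The tests named without covariates are the Welch t test for mean FEDO, the log-rank test for time to treatment completion, and the crude logistic and Cox models. None has a sex term or sex strata, and no other section brings sex back into a between-arm comparison.

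On size, the Sample Size section says "The calculated sample size is 124", then "At a 14% attrition rate, the estimated final sample size was 144 participants with 72 subjects per group", for 85% against 63% adherent.

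**The concern.** Stratified blocks force the two arms to have nearly the same mix of men and women. If sex predicts adherence, the arm difference then varies less from trial to trial than under simple randomization. An analysis that ignores sex does not know this. It leaves the between-sex variation in its error term although the design has taken that variation out of the comparison. Stratifying on a prognostic factor is therefore a reason to include it, and the protocol gives it as a reason to leave it out.

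This is an explicit rule with an explicit reason, not a detail left open. A later analysis plan could only follow it or contradict it. At stake are a test whose true size lies somewhat below 5% and the loss of whatever precision the stratification was meant to buy.

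**Working it through.** **The plan's own figure.** With 0.85 and 0.63 (mean 0.74), two-sided 5% and 80% power:

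n per arm = [1.960·√(2·0.74·0.26) + 0.842·√(0.85·0.15 + 0.63·0.37)]² / 0.22² = (1.216 + 0.505)² / 0.0484 ≈ 61.2, so 62 per arm and 124 in total, as stated. The odds ratio (0.63/0.37)/(0.85/0.15) = 0.30 also agrees. 124/0.86 = 144.2, which the plan rounds to 144. Power at 62 per arm is 80.5%. This calculation does not use sex.

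**Assumptions not in the protocol.** 60% men, men the less adherent sex, 63% adherent in control, and sex-adherence odds ratios of 1.5, 2, 3 and 5. The protocol asserts an influence of sex but gives no size, so a range is needed.

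**Variance of the unadjusted risk difference.** With balanced strata, the unadjusted analysis uses p(1−p) = 0.63·0.37 = 0.2331 per patient. The variance that actually applies is the within-sex part, 0.2331 − 0.6·0.4·Δ², where Δ is the gap between the sexes. The standard error is overstated by the square root of the ratio.

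| Sex odds ratio | Men / women adherent | Δ | Within-sex variance | Variance ratio | SE overstated by about |
|---|---|---|---|---|---|
| 1.5 | 0.593 / 0.686 | 0.093 | 0.2310 | 1.009 | 0.4% |
| 2 | 0.567 / 0.724 | 0.157 | 0.2272 | 1.026 | 1.3% |
| 3 | 0.534 / 0.775 | 0.241 | 0.2192 | 1.063 | 3.1% |
| 5 | 0.496 / 0.831 | 0.335 | 0.2061 | 1.131 | 6.3% |

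**Size and power of the test.** Simulation with exactly balanced sex strata, comparing the plain chi-square test with the sex-stratified Cochran-Mantel-Haenszel (CMH) test:

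| Sex odds ratio | Size of nominal 5% chi-square, 72 per arm | Power gained by stratifying, 62 per arm |
|---|---|---|
| 1.5 | about 4.8% | about 0.3 points |
| 2 | about 4.6% | about 0.6 points |
| 3 | about 4.2% | about 1.2 points |
| 5 | about 3.6% | about 2.1 points |

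The CMH test has size 4.8 / 5.0 / 5.0% at odds ratios 2 / 3 / 5. With the planned blocks of 4 and 6 at 144 patients, where incomplete blocks leave slight imbalance, the chi-square size is 4.7 / 4.5 / 3.6% at the same odds ratios.

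**Mean FEDO.** With normal data at 144 patients and sex gaps of 0 / 0.25 / 0.5 / 0.75 / 1 SD, the Welch test has size 4.8 / 5.0 / 4.5 / 3.6 / 2.8%. At the 1 SD gap its average standard error is 0.185 against a true sampling SD of 0.166. A linear model with sex stays between 4.8% and 5.4%.

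**Logistic model.** In the null case at 144 patients, the crude log odds ratio has a model standard error of 0.348 to 0.349. Its true sampling SD is 0.350 / 0.347 / 0.338 / 0.323 for sex gaps of 10 / 20 / 30 / 40 points. Adding sex raises the model standard error to between 0.352 and 0.383. With a true effect at 124 patients and a 20-point gap, the estimate moves from 1.235 to 1.284, its standard error from 0.455 to 0.465, and power from 80.8% to 82.3%. The gain comes from an estimate further from the null, not from a smaller standard error.

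**The case against.** The strongest objection is that the harm is conditional and probably small. The protocol gives no size for the sex effect. At an odds ratio of 1.5, a gap of about 9 points, nothing visible happens. Odds ratios of 3 and 5 mean gaps of about 24 and 34 points, which exceed the 22-point treatment effect the trial is designed to detect. Unadjusted power at 62 per arm stays at about 81% to 82% throughout, above the planned 80%. The calculations compare tests without other covariates; in the adjusted models, any listed covariate that correlates with sex would absorb part of the loss. All of this stands and limits the point to a small one. It does not rescue the stated reason.

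Several stronger readings are tempting and are not supported:

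- A reader might infer that the standard errors are definitely too large. That follows only if sex predicts adherence materially.
- A reader might infer that adding sex would narrow the odds-ratio interval. It does not: in logistic regression the standard error rises slightly, and the odds ratio becomes conditional on sex.
- A reader might infer bias or excess false positives. Leaving sex out causes neither; the error is on the conservative side.
- A reader might see a fault in adjusting for variables not used in the randomization. That is not an error in itself.

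**Conclusion.** The rule rests on reversed reasoning and conflicts with the protocol's own reason for stratifying. To the extent that sex predicts adherence, the analyses that ignore it (crude chi-square or logistic, Welch t, log-rank) are mildly conservative and lose a little power. Over sex odds ratios from 1.5 to 5, the loss runs from negligible to about 2 percentage points of power, with a true size of about 3.6% at the extreme. These figures depend on the assumed 60% men, 63% control adherence and size of the sex effect. The direction needs only that sex matters, as the protocol says it does. The planned 124 evaluable and 144 randomized patients are unaffected. This is a minor but clear error, worth correcting because correction is nearly free.

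**What to change.** Delete the sentence and its rationale. State instead that sex, as the stratification factor, is included in every between-arm analysis:

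- a sex term in a linear model for mean FEDO, in place of the unadjusted Welch comparison;
- a CMH test stratified by sex for FEDO of at least 80%;
- a sex term in the logistic and Cox models;
- a log-rank test stratified by sex.

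The cost is one sentence in the protocol, matching text in the analysis plan, and one degree of freedom per model. Recruitment, randomization and sample size do not change. The one small downside is interpretive: adjusted odds and hazard ratios become conditional on sex and should be labelled so. The change should be justified as analysing the trial as it was randomized, not as narrowing the odds-ratio interval.

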## Methods

### Trial Design

The DOT Selfie study is an open-label RCT. A total of 144 adult patients with a confirmed diagnosis of drug-susceptible TB who are initiating treatment or are within 1 month of treatment initiation at designated TB clinics will be randomized into 2 parallel groups. Of the 144 participants, 72 will be randomized into a control group to receive the usual-care DOT (UC-DOT), and 72 will be randomized into the intervention group to receive a smartphone with the VDOT app to video-record daily medication intake for review via a secure cloud system. All study participants will attend 2 monthly clinic visits at 2, 4, and 6 months (or at the end of treatment), during which clinical and sputum assessments will be performed.

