#### Follow-up of Participants With Missed Videos or Study Visits

A predefined follow-up protocol will be used to contact study participants in cases of missed doses or videos. The research staff will make 2 phone call attempts within the first 24 hours of a missed, expected video to establish dosing history and the reason for missing videos. If there is no response from the participants within 72 hours, the research team will escalate the follow-up to a field visit to trace the participant at home or work. After a period of 2 weeks from when the intensive, active follow-up protocol has been completed, there will be a waiting interval of 2 weeks, hoping that the participant will call back or return to the clinic for a routine visit. If the participant does not show up for the scheduled clinic visit, the national TB program staff will get involved in support of the patient. A declaration of “lost to follow” will be made if the participant does not return for 2 consecutive months, in line with the standard World Health Organization’s guidelines [34].

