### Study Outcomes

The primary outcome measure is the level of adherence calculated as the fraction (proportion) of expected doses observed (FEDO) over the 6 months of treatment or by the end of the study following randomization. Since direct observation as a way of measuring medication adherence may be challenging to employ consistently in the UC-DOT group, we will also use self-reports and pill counts as indirect measures of adherence and then triangulate the results. Time-to-treatment completion will be assessed as the main secondary outcome. Other outcomes will be sputum smear conversion at 2 and 6 months or the end of treatment, clinical response as a measure of self-reported improvement in TB symptoms, and weight gain at 2, 4, and 6 months or the end of treatment. Other outcomes will be self-reported side effects, the occurrence of adverse events, and patient satisfaction at the exit of the study. Patient satisfaction will be evaluated in 2 ways: (1) overall satisfaction with VDOT or UC-DOT, and (2) satisfaction with specific areas, such as the VDOT technology and app use; information and training received; interaction with treatment supporters, health providers, or research staff; and privacy and confidentiality during medication intake. Additionally, at study exit, we will conduct individual qualitative interviews for both UC-DOT and VDOT participants to capture detailed information about participant experiences during the study.

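### Median, log-rank and Cox alone for time to treatment completion do not, under usual censoring, show whether the arms differ in who completes; add cumulative incidence and the completion proportion

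*Protocol article*

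**What the plan says.** Study Outcomes ranks the endpoint: "Time-to-treatment completion will be assessed as the main secondary outcome". Statistical Analyses gives its purpose, an outcome that "can be used to compare the 2 groups according to TB program performance indicators", and names the methods: "Survival analysis to compare the median time-to-treatment completion between study groups with associated log-rank tests will be performed", then "Crude and adjusted Cox proportional hazards regression analyses will be performed to determine factors associated with time-to-treatment completion". No other analysis of completion is named.

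The article expects patients who will not complete. Loss to follow-up is a defined status; the declaration "will be made if the participant does not return for 2 consecutive months". The section on discontinuing interventions covers withdrawal, dropout and cross-over, and includes these patients in the primary intention-to-treat analysis. The adverse-event section lists loss to follow-up and death from tuberculosis as potential serious events. Sample Size assumes 14% attrition and cites a Kenyan trial with overall loss of 11.7%, split as "9.9% in the usual-care DOT arm and 1.76% in the digital intervention arm".

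On entry, Trial Design admits patients "who are initiating treatment or are within 1 month of treatment initiation". The article gives no censoring rule, competing-event rule or time origin for this outcome.

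**The concern.** Treatment is planned for about 6 months, so patients who complete tend to finish close together, and most deaths and losses come before completions begin. A patient censored in month 3 leaves the risk set and is treated as someone who would have completed like those who stayed. Death rules completion out. Loss is itself a failure to complete in the terms by which a TB programme is judged.

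An arm could therefore lose several times as many patients as the other and show the same Kaplan-Meier curve, the same median and a hazard ratio near 1. A programme reading that result as equal performance would be misled on the question that this outcome is meant to inform.

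**Working it through.** **Inputs from the article.** 72 per arm, two-sided 5% level, 14% planned attrition, cited loss of 9.9% and 1.76% (overall 11.7%).

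**The plan's own figure.** The article gives no power or event count for this outcome. Its only sample size is for the primary outcome, and it reproduces:
- n per arm = [1.96·√(2·0.74·0.26) + 0.8416·√(0.85·0.15 + 0.63·0.37)]² / 0.22² = (1.2158 + 0.5054)² / 0.0484 = 61.2. This rounds up to 62 per arm, or 124 in total.
- 124/0.86 = 144.2, against 144 stated.

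The present point does not affect that number.

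**Reading the cited loss rates.** 9.9 + 1.76 = 11.66, which is the quoted overall 11.7%. The two figures therefore look like shares of all patients. As rates within equal arms they would average (9.9 + 1.76)/2 = 5.8%, which does not fit 11.7%. If the cited trial's arms were equal (an assumption), the arm rates are double: 19.8% and 3.5%. Both readings are carried:
- Smaller scenario: loss 9.9% vs 1.76%, completion 90.1% vs 98.2%.
- Larger scenario: loss 19.8% vs 3.5%, completion 80.2% vs 96.5%.

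**Simulation (assumed distributions).** 72 per arm, 1,500 trials per scenario. Loss is uniform over days 1–179. Completion is at day 180 plus an exponential delay of mean 30 days, cut at day 270, with the same distribution in both arms. Only retention differs.

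| Scenario | Log-rank, censored at loss | Hazard ratio | Log-rank, non-completers kept at risk | Hazard ratio | Comparison of proportions |
|---|---|---|---|---|---|
| Smaller | 5.4% | 1.00 | 30% | 1.30 | 60% |
| Larger | 5.3% | 1.00 | 71% | 1.59 | 91% |
| Equal loss, 14% | 5.5% | 1.00 | 5.1% | 1.00 | 4.7% |

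The percentages are rejection rates. With censoring at loss, the Kaplan-Meier completion curve reaches 100% in both arms in every scenario. The reason is structural: all losses precede all completions, so the risk set at each completion holds only patients who will complete, and their timing is the same in both arms. Other runs put the kept-at-risk rule at 24–30% (smaller) and 65–71% (larger), or 73% in the larger scenario with a mean delay of 10 days. The normal formula for two proportions gives 55% and 87%.

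**The median.** With censoring, the medians differ by about 0 days. With non-completers kept in, half of an arm has completed at delay −30·ln(1 − 0.5/π), where π is the proportion completing:
- Smaller: 24.3 − 21.3 = 3.0 days.
- Larger: 29.3 − 21.9 = 7.4 days, or 2.5 days if the mean delay is 10 days.

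Completion differs by 8 and 16 percentage points in these two scenarios.

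**The opposite case.** Loss of 14% in both arms, mean delay 20 vs 10 days (assumed). Log-rank with censoring rejects in 95–99.8% of trials, depending on the delay distribution. Keeping non-completers at risk gives 44–73%, and comparing proportions about 5–6%.

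**The case against.** The strongest objection is that the protocol never says that deaths or losses are censored. A journal article commonly leaves such rules to the SAP or the full protocol, so their absence is no finding. The article also commits to intention-to-treat and to using information from all randomized patients. A SAP could keep non-completers at risk under the same named tests. This stands, and it rules out a reading that one might be tempted to infer: that the planned analysis cannot see a retention benefit. The documents support only the conditional statement about usual censoring.

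Second, missed doses may delay completion, and the planned log-rank test is then much stronger than a comparison of proportions, as the last case above shows. This also stands. Speed and completion are different questions, and choosing speed is not an error. The point is that the stated purpose calls for both.

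Third, the cited Kenyan rates were used only to set overall attrition; they do not predict unequal loss here. The scenarios are therefore illustrations. Taking 9.9% and 1.76% as arm rates, to set about 5% rejection against 55–60%, would lean on a doubtful reading of them.

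Fourth, one might infer bias from entry up to 1 month after treatment start. Both randomized arms share that window, so the issue is interpretability.

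Finally, this is a secondary outcome in a trial that calls itself a pilot, and the primary adherence analysis, which includes withdrawals and dropouts, may capture part of a retention effect.

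**Conclusion.** The concern holds in a limited form. The named methods, as usually run, describe how fast retained patients finish and leave unanswered who completes treatment. Under censoring at loss and equal timing, the log-rank test rejects at about its nominal 5%, even with completion of about 80% vs 96%. A rule that keeps non-completers at risk recovers part of the effect: 24–30% power in the smaller scenario and 65–71% in the larger. The conclusion thus turns on a rule that the article does not state. The median is nearly uninformative on completion under either rule.

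These sizes rest on assumed loss rates, loss times and delay distributions, and on an effect through retention alone. The sample size and the primary analysis are untouched. The change is worth making because it is nearly free, but the planned analysis is incomplete for its purpose rather than invalid.

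**What to change.** - Keep the log-rank test and Cox model, labelled as a cause-specific analysis of speed in all randomized patients. Do not restrict them to completers, which would select on an event after randomization.
- Add the cumulative incidence of completion by arm (Aalen-Johansen), with Gray's test or a Fine-Gray model. Treat death, loss to follow-up, treatment failure and withdrawal as competing events.
- Report the difference between arms in the proportion completing by a fixed, prespecified day, with its 95% confidence interval.
- State the censoring rule, and one time origin that applies to both arms.

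The cost is SAP wording and standard routines in the planned Stata and R, with no new data and no change in sample size. The downsides are one more analysis, a subdistribution ratio that is harder to explain than a Cox hazard ratio, and less sensitivity than the log-rank test to a pure timing effect. That last point is why both analyses should be reported.
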